# 6. Investigational therapy and controls

## 6.1 Acupuncture

A total of 16 treatments over 8 weeks will be administered (2/week). All study acupuncturists will be experienced, with a minimum of a Bachelors level qualification in Acupuncture and will hold current Chinese Medicine practitioner registration with AHPRA. Practitioners will be located in central and western Sydney areas. The PI ([name]) is also an acupuncturist and will train the practitioners in the trial protocol as well as delivering treatments to those women who find treatment at Campbelltown campus geographically conveneient.

Acupuncture treatment will be delivered via a fixed set of acupuncture points, based on those used in a previous pilot clinical trial using a traditional Chinese medicine (TCM) framework to treat endometriosis [14]. Acupuncture points will include Spleen 6, Spleen 8, Spleen 10, Stomach 29, Stomach 36, Ren 3, Ren 4 and Liver 3.

Acupuncture points will be needled bilaterally and needles retained for 25-30 minutes. Point location and needling depth will be as specified in *A Manual of Acupuncture* [34]. Single use, stainless steel needles of varying gauge (.20 x 30mm or .25 x 40mm), dependent on body shape, will be used.

No other TCM co-interventions (moxabustion, cupping or herbal medicine) will be allowed during the trial.

## 6.2 Control group

Participants will continue with the usual care as currently prescribed or advised by either their general practitioner or gynecological specialist. The use of usual care alone will allow the natural progression and fluctuations in CPP to be isolated from the effect of acupuncture.

## 6.3 Prior and Concomitant Medications

### 6.3.1 Permitted medications

Subjects will continue with all prescribed medication and can use analgesics as needed for pain relief.

# 7. Study Assessments

## 7.1 Safety Assessments

At each treatment session the treating acupuncturist will ask the participants if they have had any adverse events or reactions after the last treatment. Any adverse events or reactions that are thought to be causally associated with the intervention will be recorded in the practitioners log book and reported to the primary investigator [name]. Any adverse events reported to the PI will be discussed with the other investigators for clinical significance. All adverse events reported during the duration of the trial will be recorded under adverse events as part of the case report form.

Minor adverse events for acupuncture are expected to occur at a rate of around 8.6% however these were mostly minor with 2.2% requiring treatment [35]. The most common adverse events were minor bleeding or hematoma (6.1%) and pain (1.7%). Negligence or malpractice accounted for .1% of all adverse events and included broken or forgotten needles or pneumothorax. Bleeding and hematoma made up 58% of all adverse events. Neither of the two pneumothorax that occurred were life threatening. No deaths or permanent injuries were associated with the acupuncture treatments.

EEG is non-invasive research, so there is very minimal discomfort involved. It is possible that there may be a very small amount of discomfort when the electrode cap is fitted on participants' heads. The researcher will do everything possible to ensure that this experience is as comfortable for participants as possible. This will be done by ensuring that your cap is the correct size, and the researcher will check with participants throughout the experiment to ensure that the cap remains comfortable.

Participants will also be asked to provide a blood sample. The sample will be collected by a trained phlebotomist, and discomfort will be very minimal.

Participants will undergo a conditioned pain modulation test to measure the function of their descending pain systems. This test involves applying pressure stimuli to one part of the body while another part of the body is experiencing heat or cold pain. In this study we will be applying stimuli to the volar surface of the forearm. There are no risks associated with pressure stimuli. Some discomfort may be present when the pressure sensation first changes to one of pain. However, as this is a threshold test, the pressure stimulus will be ceased as soon as the participant notes that the sensation has changed from pressure to pain. There is a small risk of a burn with any application of heat. The risk of a burn will be reduced by screening and excluding participants with reduced peripheral sensation. In the unlikely event of a burn, standard operating procedure for treatment of a burn will be implemented. All staff will be familiar with these procedures.

The EEG, conditioned pain modulation and blood samples will all be taken during a single session at the same location at the National Institute of Complementary Medicine prior to receiving any trial intervention. This will be repeated at the conclusion of the trial intervention, or after 8 weeks in women who are allocated to usual care.

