# 4. Study Population

## 4.1 Sample Size

30 women in total, 15 participants per group.

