# 8. Data Collection

Baseline demographic data on age, ethnicity, menstrual history, smoking, current medication and revised American Society of Reproductive Medicine (rASRM) classification [38] of endometriosis will be collected by the primary investigator ([name]) at prior to the first acupuncture session. Baseline pain scores for both non-cyclical and menstrual pain will be collected prior to trial entry. The EXPECT questionnaire will be used to determine expectancy and belief in acupuncture.

*Primary outcome measure:*

The primary outcome measures are daily 0-10 numeric rating scale (NRS) for non-cyclical pelvic pain and a separate daily 0-10 NRS used for menstrual pain during the period itself.

*Secondary outcome measures:*

The Clinical Global Improvement (CGI) scale and The Endometriosis Health Profile (EHP-30) [36] will be used as secondary quality of life outcomes. Data will also be collected on safety, expectation, rescue medication use, presence and severity of other endometriosis symptoms (dyspareunia, dyschizia, dysuria) as well as the financial and personal impact (e.g time off work, additional help required at home) of endometriosis related symptoms. Feasibility outcomes will include an assessment of interest to participate in the trial, identification of appropriate recruitment strategies, the appropriateness of eligibility criteria, compliance with treatment attendance and data collection, and dropout rates. components of the consultation and treatment sessions were important.

*Quality assurance:*

Quality assurance measures on needling technique will be carried out on practitioners during the study period by using an independent acupuncturist to check point selection and location at least once for each practitioner.

*Biomarkers:*

Drawing of blood (IL-6) will be undertaken by PI [name] at baseline and at completion and neurological investigations (EEG and CPM) will be undertaken at baseline and again at the conclusion of treatment by PI [name] and PI [name].

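### Adverse-event enquiry is described only at acupuncture sessions, with none for usual care, after the last session or after the study procedures, and the two recording rules in Section 7.1 do not join up

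*Protocol*

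**What the plan says.** **Enquiry.** Section 7.1 describes one solicited enquiry: "At each treatment session the treating acupuncturist will ask the participants if they have had any adverse events or reactions after the last treatment". Section 6.1 sets 16 sessions over eight weeks for the acupuncture arm. For the control arm, Section 6.2 says: "Participants will continue with the usual care as currently prescribed or advised by either their general practitioner or gynecological specialist".

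**Recording.** Two rules stand in the same paragraph of Section 7.1. The first is: "Any adverse events or reactions that are thought to be causally associated with the intervention will be recorded in the practitioners log book", with a report to the primary investigator. The second is: "All adverse events reported during the duration of the trial will be recorded under adverse events as part of the case report form".

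**Status of safety.** Section 8, under secondary outcome measures, states: "Data will also be collected on safety, expectation, rescue medication use". Section 7.2 likewise lists safety among the data collected. Neither limits this to one arm.

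**Other contacts.** Both arms have the EEG, pain-modulation and blood session at baseline. On the second session, Section 7.1 says: "This will be repeated at the conclusion of the trial intervention, or after 8 weeks in women who are allocated to usual care". Section 7.2 lists what the daily diary holds (rescue medication and endometriosis symptoms), and adverse events are not among the items. Section 11.2.2 gives all participants emergency telephone numbers.

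**The concern.** A woman who is asked about adverse events twice a week will report more of them than one who is never asked. When the asking is tied to the experimental treatment, the number of events in each arm reflects the collection method as well as what happened to the women. The trial lists safety as an outcome and is meant to prepare a larger trial, so a table of adverse events by arm is a natural product of it. As the plan stands, such a table could not be interpreted.

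There are also gaps within the acupuncture arm. The question looks back to the previous treatment, so no described question covers the period after the final session. Under Section 5.5.3 a woman who withdraws is taken off treatment at once, and this also ends the only described enquiry. Dropout and acceptability are feasibility aims, so information on reactions around withdrawal would be useful to have.

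**Working it through.** The protocol attaches no figure, power or error rate to safety, so there is nothing of its own to reproduce. The check is a count of scheduled enquiries, an illustration of what unequal asking can do, and a comparison of the two recording rules.

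**1. Scheduled enquiries.** Inputs: 15 women per arm (Section 4.1: "30 women in total, 15 participants per group"); 16 sessions per woman in acupuncture (Section 6.1); no sessions in usual care.

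- Acupuncture: 15 × 16 = 240 at most.
- Usual care: 15 × 0 = 0.
- At session 1 there is no earlier treatment to look back on, so at most 15 × 15 = 225 enquiries cover a treatment. The asymmetry is unchanged.

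**2. What unequal asking can produce.** Assume the same true risk per woman in both arms, full capture when asked, and spontaneous capture *c* when not asked. Expected women with a recorded event = 15 × risk in acupuncture and 15 × risk × *c* in usual care. The 8.6% is the minor-event rate in Section 7.1, which does not say whether it is per patient or per session. Here it is read as per patient and applied to both arms purely for illustration. The other risks and all values of *c* are assumptions.

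| True risk, both arms | Acupuncture | Usual care, c = 0 | c = 25% | c = 50% |
|---|---|---|---|---|
| 8.6% | 1.29 | 0 | 0.32 | 0.645 |
| 20% | 3.0 | 0 | 0.75 | 1.5 |
| 40% | 6.0 | 0 | 1.5 | 3.0 |

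An apparent excess in acupuncture arises with no true difference. A count taken from the log book would also be affected in the other direction, because unrelated events are left out of it. The net direction of the distortion is therefore not known in advance.

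**3. Periods and procedures without a described enquiry.**

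- After the last attended session, whether session 16 or earlier: no later session at which to ask.
- After withdrawal: treatment stops, and the sessions with it.
- After blood sampling and the heat or cold test: these come before any intervention and again at its end, so a question about the time since the last treatment is not aimed at them. This holds in both arms. It is a general gap and not a further difference between arms. Section 7.1 itself acknowledges a small burn risk from the heat stimulus.

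**4. The two recording rules side by side.** The log book and the report to the primary investigator take events believed causal. The case report form takes every reported event. An event mentioned at a session but judged unrelated belongs on the form under the second rule, yet under the first it is neither logged nor passed on. No other route to the form is given.

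**The case against.** The best defence is that this is a feasibility study of 30 women. Section 2 names acceptability and adherence and does not name comparative safety, and Section 9.2 plans no safety test between arms. The safety interest in Section 7.1 is mainly in reactions to needling, which only one arm can have, and describing them in that arm alone would be legitimate. That stands as far as it goes: no stated analysis fails. But the protocol does not say that safety is one-arm and descriptive. It lists safety for the trial as a whole. How adverse events are elicited is also protocol content, so a separate analysis plan would not be expected to supply it.

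Four stronger readings are tempting, and the text does not support them.

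- *Events are kept only if the treating acupuncturist thinks them causal.* The filter applies to the log book and the report to the primary investigator. The case report form is to hold all reported events. Nor does Section 7.1 name who judges causality. The treating practitioner is a natural guess, but still a guess.
- *Unrelated events are lost.* The two sentences can be read as tiers, with related events escalated and all events put on the form. The missing route is something to reconcile and does not prove loss.
- *Usual-care women cannot report events.* No enquiry is described for them, but they attend a staffed 8-week session and hold the emergency numbers, so unsolicited reports are possible.
- *The trial would reach a false conclusion that acupuncture is acceptably safe.* The protocol sets no such criterion or conclusion.

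It would also be conjecture to say that events leading to dropout are those most likely to be missed. What can be said is that no enquiry is described after withdrawal.

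**Conclusion.** The point holds in a limited form. Followed as written, Section 7.1 gives up to 240 scheduled enquiries in one arm and none in the other. It describes no question after the last session, after withdrawal or after the study procedures. Any set of safety counts by arm would mix true differences with unequal ascertainment, and the data could not separate the two. The log-book rule and the case-report-form rule fit poorly together, because no route is given for events judged unrelated.

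This rests on reading the protocol's silence on usual care as no planned enquiry. If the 8-week assessment or the case report form already includes an adverse-event question, most of the point reduces to stating it in Section 7.1. The counts of enquiries come from the protocol. The expected counts of events are illustrations under stated assumptions and are not predictions. The change is worth making before recruitment, because information that was never asked for cannot be recovered at analysis.

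**What to change.** - Add one adverse-event item to the daily diary in both arms, and ask the same question at the existing end-of-study assessment in both arms. Word it so that it covers the blood draw and the pain test as well as treatment, and state that it is also asked of women who withdraw, where they agree.
- Record every event whatever its presumed cause, with relatedness as a separate field, and name the role that makes that judgement.
- Reconcile the log-book sentence and the case-report-form sentence in Section 7.1 so that each reported event has a stated route to the form.
- At minimum, if none of this is adopted, state that safety is descriptive for the acupuncture arm only and will not be compared between arms.

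The cost is one extra diary item, slightly more data entry and a wording change in Section 7.1. No added visit is needed.

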## 4.3 Inclusion Criteria

- Women aged 18-45
- have a laparoscopic diagnosis of endometriosis in the last 5 years as per current clinical guidelines [30-32]
- having regular menstruation
- the presence of at least one of the following: dysmenorrhea, dyspareunia, dyschezia or dysuria rated >= 4/10 on a numeric rating scale.

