## 4.4 Exclusion Criteria

## endometriosis surgery within the past 6 months,

## started oral or injectable contraceptive pill, GnRH-a or danazol within the last 6 months.

# 5. Participant selection and enrollment

## 5.1 Identifying participants

Recruitment will be primarily via Endometriosis Australia, Endoactive and Pelvic Pain foundation of Australia, all not for profit charities. Trial information and invitations to participate will be published on their respective websites as well as via their Facebook pages and twitter feeds. Recruitment will also occur via targeted Facebook advertising

5.2 Screening for eligibility:

For women expressing interest in the study they will make contact with the co-ordinating centre. Initial screening will be undertaken over the phone by the researcher. For those women that pass the initial screening, they will be invited to fill in a daily pain diary for four weeks to confirm eligibility and to provide baseline pain data.

To participate in the EEG sub-study women need to not meet any of the following criteria:

- Diagnosed psychiatric disorders including: dissociative disorder, obsessive-compulsive disorder, personality disorder, schizophrenia, bipolar disorder
- History of drug and alcohol dependence or substance-related disorders
- History of seizures
- Head trauma with loss of consciousness
- Left-handedness

If women meet any of these criteria they will not have EEG measurements performed but all other components of the study remain the same.

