5.5.2 Treatment allocation

Randomization will be 1:1 into one of two study groups:

Manual acupuncture + usual care:

Women in this group will receive 16 acupuncture treatments over 8 weeks (twice weekly – with a minimum of 2 days between treatments) in addition to their usual care, delivered by registered Chinese medicine practitioners in private clinics or at the clinic room (5.LG.07) at the National Institute for Complementary Medicine. Manual acupuncture will be delivered using a semi-standardized protocol based on previous research [14, 33].

Usual care:

Participants will continue with the usual care as currently prescribed or advised by either their general practitioner or gynecological specialist. Usual care will be based on specific medical advice that has been given to the participant, but commonly involves the oral contraceptive pill or non steroidal anti inflammatories or analgesic medication.

5.5.3: Withdrawal procedures

If a participant wishes to withdraw from the trial they will be immediately removed from treatment.

If a participant withdraws during intervention they will not be replaced however if they withdraw post randomization but prior to the first treatment they will be replaced.

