## 7.2 Study assessments

Key outcomes will be assessed at baseline and at the end of the intervention. Drawing of blood (IL-6) and neurological investigations (EEG and CPM) will be undertaken. Pain outcomes will be based on daily numeric rating scale (NRS) for non-cyclical pelvic pain and a separate NRS for menstrual pain. The Clinical Global Improvement (CGI) scale and The Endometriosis Health Profile (EHP-30) [36] will be used as secondary quality of life outcomes. Financial and personal impact of endometriosis will be collected via the ENDOCOST questionnaire [37]. Data will also be collected on safety and expectation (using the EXPECT questionnaire).Daily data on rescue medication use, presence and severity of other endometriosis symptoms (dyspareunia, dyschizia, dysuria) will be collected on the daily pain diary. Feasibility outcomes will include an assessment of interest to participate in the trial, identification of appropriate recruitment strategies, the appropriateness of eligibility criteria, compliance with treatment attendance and data collection, and dropout rates.

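### The second marker session has a different anchor in each arm with no common window or cycle-day record, and the four-week baseline diary can miss the period

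*Protocol*

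**What the plan says.** **Marker sessions.** Section 7.1 places the first EEG, CPM and blood session "during a single session at the same location at the National Institute of Complementary Medicine prior to receiving any trial intervention". For the second it says: "This will be repeated at the conclusion of the trial intervention, or after 8 weeks in women who are allocated to usual care". It does not say from which day the 8 weeks are counted. Section 8 says the neurological tests "will be undertaken at baseline and again at the conclusion of treatment", and section 7.2 says: "Key outcomes will be assessed at baseline and at the end of the intervention". Neither gives a rule for women who receive no treatment course.

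**Course length.** Section 6.1 plans 16 sessions at two a week over 8 weeks. Section 5.5.2 adds a spacing rule, "with a minimum of 2 days between treatments". This is a lower limit only. No section states an upper limit on course length or a visit window.

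**Cycle.** Section 4.3 requires "having regular menstruation" and gives no range of cycle length. No section records cycle day at a marker session.

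**Baseline diary.** Under section 5.2, women who pass telephone screening are told that "they will be invited to fill in a daily pain diary for four weeks to confirm eligibility and to provide baseline pain data". One of the two primary outcomes in section 8 is a daily pain score given only while the woman is menstruating.

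**The concern.** Section 6.2 gives the purpose of the usual-care arm: to separate the natural course and fluctuation of pain from the effect of acupuncture. That works for the markers only if both arms are measured at the same distance from baseline. An event anchor in one arm and a calendar anchor in the other make this depend on attendance, which is itself one of the feasibility unknowns.

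If a marker varies over the cycle, a change in cycle phase between the two sessions enters each woman's change score. With 15 women per arm, that variance is costly, and it cannot be examined later unless cycle day was written down. IL-6 is the most exposed marker, because section 9.2 assesses its change with a paired t-test. Such a test looks only at within-woman change, so no control comparison removes an effect of time or phase.

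The diary is a separate matter. It is a fixed calendar window, yet it supplies the baseline for an outcome that exists only on menstrual days. It also confirms eligibility, so a woman who qualifies through dysmenorrhea alone could finish it with no period on which to confirm that.

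**Working it through.** **Inputs from the protocol:** 16 sessions at 2 per week (6.1); usual care measured after 8 weeks (7.1); diary of four weeks, 28 days (5.2); regular menstruation (4.3); 15 women per group (4.1).

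**Assumptions, not in the protocol:** cycle lengths L up to 35 days, a 5-day period (4 and 7 days as a check), and a diary that starts on a random cycle day.

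**1. Planned timing.** 16 / 2 = 8 weeks, which reproduces the protocol's own figure. On schedule the two arms nominally coincide. If sessions fall on days 0 and 3 of each week, the last is on day 7 × 7 + 3 = 52, which is 4 days before day 56. So the planned gap is 0 to about 4 days. A larger gap needs slippage, early stopping or clocks that start on different days. Two sessions re-booked at the end, at 2 per week, add about one week.

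**2. Cycle-day shift and diary capture.**
- Shift at day 56 = the smaller of (56 mod L) and (L − 56 mod L).
- A complete 5-day period must start on one of the first 24 diary days, so P(no complete period) = 1 − 24/L for L of 24 or more.
- When L exceeds 28, the diary omits L − 28 consecutive cycle days, and P(fewer than five menstrual days) is also 1 − 24/L. When L is 28 or less, every cycle day is covered and this probability is 0.
- P(no menstrual day) = (L − 32)/L when L exceeds 32, otherwise 0.
- Longest extension to reach a complete period = L + 4 − 28 days.

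| L (days) | Shift at day 56 | No complete period | Fewer than 5 menstrual days | No menstrual day | Longest extension |
|---|---|---|---|---|---|
| 24 | 8 | 0% | 0% | 0% | 0 |
| 26 | 4 | 8% | 0% | 0% | 2 |
| 28 | 0 | 14% | 0% | 0% | 4 |
| 30 | 4 | 20% | 20% | 0% | 6 |
| 32 | 8 | 25% | 25% | 0% | 8 |
| 35 | 14 | 31% | 31% | 9% | 11 |

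At 26 and 28 days, a diary with no complete period still holds all five menstrual days, split over two bleeds. Checks at L = 35: with a 4-day period, 28.6% have no complete period and 11.4% no menstrual day; with a 7-day period, 37.1% and 2.9%.

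**3. What a phase shift does to a change score.** I assumed a sinusoidal cycle effect and cycle lengths with mean 29 and SD 2.5 days, clipped to 21–35. Results are in units of the cycle amplitude.
- *Baseline session on a random cycle day:* the mean change is about 0 whether the second session is on time, 4 days early, or 7 or 14 days late. The SD of the change is 0.69 on time, 0.91 when 4 days early, 0.86 when 7 days late and 1.16 when 14 days late.
- *Baseline sessions clustered on cycle days 5–9:* the mean change is −0.54 on time and −1.22 when 14 days late. A 14-day slip in one arm only would then separate the arms by 1.22 − 0.54 = 0.68 amplitudes.

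Phase is therefore mainly added variance. It becomes a between-arm bias only if baselines cluster by phase and the arms are also timed differently. In an uncontrolled paired test, clustering alone is enough.

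**The case against.** **The arms are both measured at 8 weeks.** This stands for the plan as written. A reader might infer from section 7.1 that the arms are timed differently by design, but sections 5.5.2 and 6.1 both plan an 8-week course. What remains is that nothing in the protocol keeps the arms together once attendance departs from schedule.

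**Not every marker change is affected.** This also stands. A reader might infer that time and phase confound all marker changes. A woman with a 28-day cycle measured on day 56 has no shift, and with baselines on random cycle days the average effect is about nil.

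**The menstrual-pain baseline cannot be biased by follow-up timing.** Correct: section 5.3 has baseline data collected before randomisation, by the same diary for everyone. Its weakness is sparse or missing menstrual days in longer cycles, not imbalance between arms. The 14% at 28 days should not be read as lost data either, since all five menstrual days are recorded.

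**The protocol does not show that these markers vary over the cycle.** True. It calls the pain cyclical in section 1.1 but gives no cycle variation for IL-6, EEG or CPM, so no effect on an outcome can be sized.

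**Cycle day may be recoverable, and covariates belong in an analysis plan.** Partly right. Menstrual history and daily menstrual scores are collected, so cycle day might be derived if the diary covers both sessions. The protocol does not ensure that, and an analysis plan cannot restore a day or a period that was never recorded.

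**This is a 30-woman feasibility study.** That limits the weight of the point. It does not remove it, because finding which markers change is a stated objective and the remedies need no extra visit.

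**Conclusion.** The point holds in a limited form, as an inexpensive improvement to data collection.

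- **Marker sessions:** the anchors differ, the origin of the 8 weeks is not named, there is no common window, and cycle day is not recorded. The consequence is a possible time imbalance (0 to about 4 days on schedule, more with slippage) and avoidable variance in marker changes. The paired IL-6 test is the least protected. The cycle-day shift ranges from 0 days (28-day cycle) to 14 days (35-day cycle). Its effect on any marker cannot be computed from the protocol.
- **Baseline diary:** with a 5-day period and a random start, 25% of women with 32-day cycles and 31% with 35-day cycles have no complete period, and 9% with 35-day cycles have no menstrual day. With cycles of 28 days or less, all five menstrual days are captured. How many of the 30 women this touches depends on their cycle lengths, which the protocol does not give.

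A reader might also conclude that the second session must be matched to the woman's baseline cycle phase. The documents do not support making that mandatory. The matching day nearest day 56 is day 2 × 24 = 48 for a 24-day cycle, before the planned course is complete, and day 2 × 35 = 70 for a 35-day cycle, two weeks after day 56. That would exchange phase noise for variable time since treatment.

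**What to change.** 1. **Diary (5.2).** Run the baseline diary for at least four weeks and until one complete period has been recorded. Cost: a longer run-in for some women, up to 4 more days for a 28-day cycle, 8 for a 32-day cycle and about 11 for a 35-day cycle.
2. **Cycle day (7.1 and 8).** Record the first day of the last period, and hence cycle day, at both marker sessions. Use it as a covariate in a sensitivity analysis. Cost: one question per session.
3. **One clock (7.1, 7.2 and 8).** Name one origin for both arms and one stated window around week 8 for the second marker session. Reconcile this with sections 7.2 and 8, which refer only to the end of treatment, and say what applies when a course has not finished or has stopped early. Cost: slightly tighter scheduling. This concerns when measurements are taken and leaves the treatment schedule as it is.

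None of the three adds a visit.
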